Given that the limitations of cognitive training for older adults with MCI reported by previous researches, we developed a process-based multi-tasks cognitive training program based on the process model (29, 30),****which was targeted to improve the executive function of older adults with MCI. The primary aim of this study is to evaluate whether the process-based multi-task cognitive training program would provide better results on executive function in older adults with MCI. The secondary aim is to explore whether potential training effects will be able to generalize to other untrained cognitive domains (transfer effects), and those effects will be maintained effectiveness over 3 months of follow-up (maintaining effect). The tertiary aim is to explore the changed performances of brain neural activity underlying the process-based cognitive training targeting at executive function.

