### Study Intervention

#### Implementation of the Cognitive Training Program

Participants in the cognitive training group will receive 10 weeks of the process-based multi-task cognitive training program with 60 min group training sessions (a small group of six participants) each given three times per week. This cognitive training program consisted of eleven training tasks in total, with a varying degree of overlap between tasks. The tasks are divided into three categories: 1) warm-up exercise; 2) practice in order; and 3) expanding training (**Table 2**). The task of warm-up exercise lasting 10 min, practice in order and expanding training tasks lasting 50 min. All cognitive tasks are completed within a medical university setting supervision of postgraduate in Master of Nursing Specialist. The program ensures that the ratio of a participant-to-researcher is no greater than 6:1 (6 participants per researcher). Each training task for all nursing specialists was randomly assigned. During the training period, the participant will have an identical training schedule. To balance the social-interaction effect, participants in the cognitive training group participated in the same health education program as the wait-list control group. Participants were reminded via smartphone to complete their training program if missing over 2 weeks. Besides, we develop a training paper record form, and the training record can be checked.

**Table 2 T2:** Tasks of process-based multi-task cognitive training program.

Categories	Tasks	Targeted domain	Difficulty levels/rounds	number of hours	A brief description of the tasks
Warm-up exercise	Recall the names	Memory	0/20	10min	Firstly, introduce yourself one by one (i.e., name, age, occupation). Then, inform participants to remember these names. The participants are asked to write down the names of the other five on white paper according to their memory at the end of cognitive training.
	You act I guess	Working memory	0/1		Firstly, participants were divided into three groups of two. Then, one participant facing the audience uses the most accurate body language to express the meaning of words, while other participants with their backs to the audience are asked to guess those words. Each group is limited to 2 min.

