#### Study Procedure

Participants will be enrolled from the nearby community health service centre via open recruitment through paper flyers, online forums, and word-of-mouth. Participants who interested in this program will be invited for an in-person interview to complete a screening questionnaire in the community health service centre, including demographic characteristics, MMSE, MoCA, ADL, and Achromatopsia anomalous trichromatic test (AATT). A trained physician in community health service centre will invite the potential participants to undergo a physical examination and neurologic diagnosis of MCI. Participants who met the eligibility criteria will be assessed with a baseline assessment and then given the EEG evaluation in the 2 days preceding the start of the cognitive training.

After that, according to the random allocation sequence, participants will be randomly assigned to one of two groups with a targeted assignment ratio of 1:1. The random allocation sequence with a block size of four will be generated using a computer randomization list by an independent researcher assistant. The random allocation sequence is sealed in opaque envelopes by an assistant. The cognitive training group will receive cognitive intervention and health education, whereas the wait-list control group will only receive health education during the research period. During the 3 months follow up, the cognitive training group and wait-list control group will receive no interventions. Complete all outcome assessments, participants in the wait-list control group will be permitted to undergo the process-based multi-task cognitive training program. Although it was not initially the plan, the health education manual for mild cognitive impairment will be provided for participants who are not finishing the cognitive training or health education through various means, such as email, public platform, and short messaging service. All outcome measurements will be assessed at baseline, 10 weeks and 3 months follow up. Study assessments and timelines are illustrated in **Table 3**.

**Table 3 T3:** Summary of study assessments and timelines.

Time point	Measurement	Post-allocation					Mode of Administration
		Baseline	Training sessions	10 weeks assessments		Follow-up 3 months	
		T0		T1		T2	

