The secondary outcome measures include neuropsychological assessments, transfer effect and electroencephalogram acquisition. Neuropsychological assessments are as follows: (1) the composite z score for the overall cognitive function, including the questionnaire of MoCA (38); (2) the Psychomotor speed, which will be accessed by Finger Tapping Test (37) and Reaction Time test (39). The transfer effects measure consist of fluid reasoning and working memory. Two tasks will be used to measure working memory: digit span forward and backward from the Wechsler Adult Intelligence Scale-Revised. Raven’s Advanced Progressive Matrices (RAPM) will be used to assess fluid reasoning. The electroencephalogram data will be recorded and collected using the Emotiv EPOC® Headset (EMO-EPO-BT9X-03) with 14 channels mobile (AF3, F7, F3, FC5, T7, P7, O1, O2, P8, T8, FC6, F4, F8, and AF4) and two references (CMS/DRL references at P3/P4; left/right mastoid process alternative). The parameters are as follows: the sampling rate is 128 Hz, the resolution is 14 bits with 1 LSB (= 0.51μV), and bandwidth is 0.16–43Hz (digital notch filters at 50Hz and 60Hz). The recording time will last approximately 5 min. The participants will be required to close and open their eyes for 30 s, respectively. During data acquisition time, the participants will be told not to move their hands and other parts of the body (40).

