#### Statistical Considerations

The primary and secondary outcome measures were analyzed using data from the intention-to-treat. Moreover, the protocol set principle was defined as those participants or the participants who completed at least 80% adherence to the program initially formulated and assessments all the required will be included. We will compare the characteristics of the completed participants versus dropout ones. Sensitivity analyses of completed participants will be further performed to explore the potential for dropout participants, and the results will be categorized as bias. Listwise deletion will be adopted to estimate treatment effects and sensitivity of the cluster dropout if missing values satisfy the criteria of the losing data entirely at random; otherwise, multiple imputation data strategies will be adopted.

Data processing and statistical analysis will be conducted using SPSS 21.0 and MatLab (The Mathworks Inc. 2016). Descriptive statistics will be reported as frequencies for categorical variables and means ± standard deviations for continuous variables. The adoption mainly the method of exploratory analysis to examine the distribution state of data. The proportionality of baseline data for both groups is compared by the non-parameters Wilcoxon test, chi-square test, and t-test. Regarding the primary outcome, a repeated ANOVA test will be used to evaluate the differences of changes and long-term effect in outcome measurement index performance in the cognitive training group and the wait-list control group, within-group over time, and interaction effects. The simple effect analysis will be added when there is an interaction between intervention factors and time factors. Secondary outcomes will be analyzed using similar statistical methods. The mediating effect model was used to test the transfer effect of cognitive training on untrained cognitive domains, with cognitive training as the mediator. A significant statistical will be considered as P < 0.05 for all comparisons. The effect size (r) was calculated using Cohen’s d to estimate the between-group effect sizes.

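### The analysis named for transfer makes the randomised training its own mediator, and one of the two transfer domains is also listed as a training target

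*Protocol article*

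**What the plan says.** The Background section sets the secondary aim: to "explore whether potential training effects will be able to generalize to other untrained cognitive domains (transfer effects"), and to see whether effects last over the 3-month follow-up.

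Outcome Measurement defines the transfer domains: "The transfer effects measure consist of fluid reasoning and working memory". Raven's Advanced Progressive Matrices (RAPM) measures fluid reasoning. For the other domain, "Two tasks will be used to measure working memory: digit span forward and backward from the Wechsler Adult Intelligence Scale-Revised". The same section counts the transfer effect among the secondary outcomes, and Table 3 schedules both measures at baseline, 10 weeks and 3 months.

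Statistical Considerations gives the primary outcome a repeated ANOVA with group, time and interaction, and says that secondary outcomes get similar methods. It then adds an analysis for transfer specifically: "The mediating effect model was used to test the transfer effect of cognitive training on untrained cognitive domains, with cognitive training as the mediator".

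Study Procedure makes clear what is randomised: "participants will be randomly assigned to one of two groups with a targeted assignment ratio of 1:1", and "The cognitive training group will receive cognitive intervention and health education, whereas the wait-list control group will only receive health education during the research period".

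Table 2 gives working memory as the targeted domain of the warm-up task "You act I guess".

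**The concern.** A mediator is a variable measured after randomisation that the exposure changes and that in turn affects the outcome. Cognitive training is what the trial assigns, so it is the exposure. The sentence names no other exposure, and it does not name the gain in executive function as the intermediate step, although that gain is what transfer is supposed to follow from.

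Two things are at stake. First, the one analysis the article ties to transfer by name would give no interpretable indirect effect. The analyst would then have to choose a different mediator later, possibly with the data in view. Second, a gain on digit span could be reported as generalisation to an untrained domain, although the programme's own task table lists that domain as a target.

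**Working it through.** The plan gives no numerical figure for this analysis, so there is none to reproduce. The check takes each possible meaning of the sentence in turn. It uses 46 participants per arm (sample-size paragraph) and an outcome SD of 1.

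**Standard mediation equations**

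- M = i₁ + a·X + e₁
- Y = i₂ + c′·X + b·M + e₂
- Indirect effect = a·b; direct effect = c′; total effect = c′ + a·b

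**Reading 1: X is allocation, M is cognitive training received as assigned.** Then M = X, so a = 1 with no residual. The second equation collapses to Y = i₂ + (c′ + b)·X + e₂. Only the sum c′ + b can be estimated. With 46 per arm the matrix [1, X, M] has rank 2 where 3 is needed. A direct effect of 0.5 with b = 0 fits exactly as well as a direct effect of 0 with b = 0.5. The one estimable quantity is the total effect, which is simply the between-arm difference.

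**Reading 2: X is allocation, M is the share of sessions attended, 0 in controls.** This can be estimated, but b is identified only from differences in attendance within the training arm. With attendance A uniform on an assumed range, mean μ and variance σ² = (range width)²/12:

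- VIF ≈ 1 + μ²/(2σ²)
- SE(b) ≈ 1/√(46·σ²)
- SE(a·b) ≈ μ·SE(b), ignoring the small error in a

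| Assumed attendance | μ | σ² | VIF | SE(b) | SE(a·b) |
|---|---|---|---|---|---|
| 95–100% | 0.975 | 0.000208 | about 2,280 | 10.2 SD | 10.0 SD |
| 80–100% | 0.90 | 0.00333 | about 122 | 2.6 SD | 2.3 SD |
| 50–100% | 0.75 | 0.0208 | about 14.5 | 1.0 SD | 0.77 SD |

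Simulation at 46 per arm gave median VIFs of about 2,339, 125 and 15, and SE(b) of 10.3, 2.6 and 1.0 SD, in agreement. For scale, the trial's planning effect on executive function is 0.575 SD, smaller than the standard error of the indirect effect even in the widest range. Attendance is also not randomised, and this model describes a dose relation, not a carry-over of gains between domains.

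**Reading 3: X is some baseline characteristic, M is training.** Training is allocated at random, so the expected a-path from any baseline variable is zero. The indirect effect is then zero by design.

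**Reading 4: the gain in executive function was meant as mediator.** This is coherent and can be fitted, but it is not what the sentence says. It addresses how transfer arises. Whether transfer occurs is still the total between-arm effect.

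**Labels for working memory, side by side**

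| Place | How working memory appears |
|---|---|
| Outcome Measurement | One of two transfer domains |
| Background; Statistical Considerations | Transfer domains described as untrained |
| Table 2 | Targeted domain of one warm-up task |

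The warm-up is one of the programme's three task categories, so the task is part of training. It is coded 0/1: no difficulty level, one round. Three pairs at up to 2 minutes each make 3 × 2 = 6 minutes, within a 10-minute block of a 60-minute session. By contrast, six of the eight cylinder tasks are coded with 64 rounds. Fluid reasoning is not listed as a target of any task.

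**The case against.** The strongest reply is that transfer already has an ordinary test. Transfer is a secondary outcome, and Statistical Considerations applies methods similar to the repeated ANOVA to secondary outcomes under intention-to-treat. RAPM and digit span are measured at all three time points, so a group-by-time comparison is available for both. This stands. A reader might infer from the mediation sentence that the secondary aim has no valid test; the document does not support that.

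A second reply is that the sentence names no exposure, so perfect collinearity follows only if allocation is supplied as the exposure. The sentence may be a garbled reference to training gain. This also stands, as a limit: the collinearity is conditional. It does not rescue the sentence, because each of the first three readings fails and the fourth needs a different variable to be named.

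A third reply is that the programme's stated target is executive function, that one single-round charades task bears little resemblance to digit span, and that the Discussion itself expects transfer to be greatest where tasks share processes. This stands on weight. A reader might infer that half of the transfer battery is invalid; that would count labels rather than measure bias, and nothing in the document allows an effect of this task on digit span to be estimated. The contradiction between the labels remains.

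**Conclusion.** The concern holds in limited form. The analysis named for transfer is mis-specified: the randomised intervention cannot mediate its own effect, and no other exposure is given. If allocation is the exposure, direct and indirect effects are inseparable (rank 2 of 3). If attendance is substituted, the standard error of the indirect effect runs from about 0.8 to 10 SD under the assumed attendance ranges. These ranges are assumptions, since the article gives no attendance figures. The repeated ANOVA still supplies a between-arm comparison on both transfer measures.

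Separately, working memory is called untrained in one place and listed as a target in another. The overlap is one brief task, which justifies relabelling digit span and no more.

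Severity is moderate: the primary outcome, sample size and primary analysis are untouched, and the aim is worded as exploratory.

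**What to change.** 1. Replace the mediation sentence with a statement that transfer is tested by the between-arm (group-by-time) comparison on RAPM and digit span at 10 weeks and at 3 months, preferably adjusted for the baseline score of each measure.
2. If mediation is kept, label it exploratory and name all three variables: allocation as exposure, change in the executive-function composite as mediator, and the transfer score as outcome. State that the mediator-to-outcome path is not protected by randomisation.
3. Reconcile Table 2 with the outcome section: report digit span as near transfer, or as a partly targeted domain, and keep the word untrained for fluid reasoning.

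The cost is about one paragraph of wording. All variables are already scheduled at the three time points, so no new data are needed. The downside is a slightly narrower claim about transfer.

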### Outcome Measurement

Data evaluators and training practitioners are blinded to group assignments. All outcome measures are assessed at baseline, immediately after 10 weeks of training, and again at follow-up 3 months after the end of cognitive training. Three trained research assistants, with a minimum of 2 years’ experience conducting mental health nursing and neuropsychological assessments, conducted a set of outcome measures. A more detailed account of study assessments and timelines are illustrated in **Table 3**.

The primary outcome measure is the composite z score executive function, which will be accessed by Trail Making Test A-B (TMT A-B), Stroop test (using software, E-Prime 2.0.10.42), and Purdue pegboard test (PPT, Lafayette Instrument Model 32020A). The selection of cognitive evaluation measures, directly relating to the target cognitive field of training, can improve cognitive training power, efficacy and increase accuracy (34, 35). Furthermore, previous studies have shown that the use of TMT A-B, Stroop tests, and PPT as executive function outcome measures in clinical trials of MCI (36, 37). We will calculate z-score composites from normalized raw data for each item and its score as a sum of all domains.

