There are some limitations to the current study. First, the sample population in this study may not represent the overall characteristics of individuals with MCI. In this study, older adults with MCI who have colour blindness would be excluded. Thereby the result will be limited in informing the cognitive benefit generalisability. Second, considering the feasibility, we do not set up an active control group, which may compromise the statistical power. Third, the follow-up cognitive training in this study was limited to 3 months because we will provide compensable training for the wait-list control group after the follow-up period. Hence, conclusions regarding the longer follow-up effectiveness of the process-based multi-task cognitive training program could not be drawn. Future study should further explore the above research gaps.

In summary, our cognitive training program, implemented by socket cylinder and use of dynamic and hierarchical tasks (the difficulty increases as the participants’ performance improves), is easy to complete in older adults with MCI. This use dynamic and hierarchical tasks and multi-modal testing (paper-pencil, computer) will not only provide reliable data on cognitive training and transfer effects but also assure compliance and motivation of participants. The training program is valid, and the effects of training can be sustained will play a vital role in the application of cognitive training in the elderly with MCI. If proven effective, the results of this protocol will be relevant to community health workers to adopt a more cost-effective and feasible cognitive training method for improving the cognitive status, executive function, psychomotor speed, and non-trained cognitive domains.

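### An unadjusted P < 0.05 covers every secondary, transfer and EEG outcome without marking them exploratory, while the Discussion anticipates conclusions on those domains

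*Protocol article*

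**What the plan says.** All references are to the protocol article.

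- **Primary outcome.** Outcome Measurement names one variable: "The primary outcome measure is the composite z score executive function".
- **Secondary family.** The same section states: "The secondary outcome measures include neuropsychological assessments, transfer effect and electroencephalogram acquisition". The components are MoCA, two psychomotor tests, digit span forward and backward, Raven's matrices and EEG. The Methods part of the Abstract names two EEG parameters, slowness and complexity.
- **Testing rule.** Statistical Considerations states "Secondary outcomes will be analyzed using similar statistical methods" and then "A significant statistical will be considered as P < 0.05 for all comparisons". The method for the primary outcome is a repeated-measures ANOVA with a group-by-time interaction, and simple effects are examined only where there is an interaction. A mediation model is added for transfer. Nothing orders the secondary outcomes, makes them depend on the primary result, adjusts them or confines them to description.
- **Status of the aims.** The Objective and Results parts of the Abstract, the aims at the end of the Background and the paragraph on transfer in the Discussion all describe the long-term and transfer questions as something to be explored. The Background makes neural activity a tertiary aim.
- **Anticipated conclusion.** The last paragraph of the Discussion says that, if the training proves effective, the results will be relevant to community health workers adopting a "more cost-effective and feasible cognitive training method for improving the cognitive status, executive function, psychomotor speed, and non-trained cognitive domains".

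**The concern.** The testing rule and the anticipated conclusion fit together badly. Under the rule, each secondary, transfer or EEG comparison with P < 0.05 is significant in the same sense as the primary comparison, whatever the primary shows. The Discussion then names the domains of those outcomes among the expected benefits. The exploratory wording of the aims would normally stop an isolated secondary P value from carrying such a conclusion, but the analysis section does not repeat it.

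Transfer is part of the stated secondary aim. With several measures each tested at 5%, a chance finding somewhere in the family is much likelier than 5%, and nothing in the analysis section stops it from being presented as an effect of training.

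**Working it through.** **Plan's own figure.** The article states no family-wise error rate. Its only figure is 0.05 per comparison, which is the error rate for a single test.

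**Step 1: count the measures.** Take one group-by-time test per measure.

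- Overall cognition: one measure, "the composite z score for the overall cognitive function, including the questionnaire of MoCA (38").
- Psychomotor speed: two measures, "which will be accessed by Finger Tapping Test (37) and Reaction Time test (39").
- Working memory: two measures, from "Two tasks will be used to measure working memory: digit span forward and backward". It is one measure if digit span is scored as a single test, as Table 3 lists it.
- Fluid reasoning: one measure, Raven's matrices.
- EEG: two parameters, slowness and complexity.

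Without EEG: 1 + 2 + 1 + 1 = 5, or 1 + 2 + 2 + 1 = 6. With EEG: 5 + 2 = 7, or 6 + 2 = 8.

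**Step 2: independent tests, all nulls true.** The chance of at least one significant result is 1 − 0.95^k:

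- k = 5: 1 − 0.95^5 = 22.6%
- k = 6: 1 − 0.95^6 = 26.5%
- k = 7: 1 − 0.95^7 = 30.2%
- k = 8: 1 − 0.95^8 = 33.7%

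**Step 3: correlated tests.** The article gives no correlations, so a common value ρ is assumed and varied from 0 to 0.8. For k equicorrelated normal statistics tested two-sided at 0.05,

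rate = 1 − ∫ φ(u) [Φ((1.96 − √ρ·u)/√(1−ρ)) − Φ((−1.96 − √ρ·u)/√(1−ρ))]^k du.

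| k | ρ = 0 | ρ = 0.3 | ρ = 0.5 | ρ = 0.8 |
|---|---|---|---|---|
| 5 | 22.6% | 20.9% | 18.3% | 12.7% |
| 6 | 26.5% | 24.1% | 20.7% | 13.9% |
| 7 | 30.2% | 27.1% | 23.0% | 14.9% |
| 8 | 33.7% | 30.0% | 25.0% | 15.7% |

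The normal statistic stands in for the interaction test. The ρ = 0 column does not depend on that choice.

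**Step 4: errors towards benefit only.** A false claim of improvement needs the error to fall on the favourable side, which has probability 2.5% per two-sided test. For this step each test is treated as a single contrast with a direction. Independent tests give 1 − 0.975^k: 11.9% for k = 5 and 18.3% for k = 8. At ρ = 0.8, dropping the lower-tail term from the integral gives 6.4% for k = 5 and 7.9% for k = 8. The range is about 6% to 18%, against 2.5% for one test.

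**Step 5: the primary outcome.** It is one composite. The number of secondary tests does not enter its error rate.

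**The case against.** The strongest reply is that these outcomes are already exploratory. The article says so in several places, there is one primary outcome, and leaving exploratory secondary outcomes unadjusted is common practice. A detailed multiplicity scheme may also sit in a full protocol or analysis plan that is not shown. Much of this stands, and it is why the point is about wording rather than a failure of the main test. It does not remove the point. The article does not leave the matter open: it states a threshold for all comparisons, and the exploratory label is absent where the threshold is set.

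The Discussion sentence is also conditional, speaks only of relevance to community health workers and does not name EEG. The Discussion part of the Abstract ties the headline conclusion to executive function. That stands too. A reader might infer that the protocol commits itself to benefit claims on every secondary domain. The text supports only the weaker statement that it anticipates such conclusions.

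Other stronger readings are tempting:

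- A reader might put the false-positive chance at about 25%. That is one cell of the table (k = 8, ρ = 0.5), and it counts EEG and errors in both directions. The article fixes neither the count nor the correlation, so only the range can be defended.
- A reader might test each outcome at both visits, giving 16 tests and, with assumed correlations of 0.5 between endpoints and 0.6 between visits, about 40%. The plan examines simple effects only after an interaction, so that figure does not describe the plan.
- A reader might assume that transfer is claimed if any one transfer measure is significant. The article states no such rule and names a mediation model as its test of transfer.

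**Conclusion.** The point holds as an inconsistency between the testing rule, the exploratory status of the aims and the anticipated conclusion. With all nulls true and one group-by-time test per measure, the chance of at least one significant secondary, transfer or EEG result is about 13% to 34%, or about 6% to 18% counting only errors towards benefit. These figures rest on a count of five to eight measures and an assumed common correlation of 0 to 0.8. The mediation model is not counted. A reader might infer that the trial's main result is compromised; it is not, because the primary test concerns a single composite. The change is worth making because it costs little and stops an isolated secondary P value from supporting adoption of the training for domains on which the trial makes no controlled claim.

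**What to change.** 1. In Statistical Considerations, reserve the claim of significance at P < 0.05 for the primary executive-function composite. Label all secondary, transfer (including the mediation model) and EEG results exploratory, and report them with estimates and 95% confidence intervals.
2. In the last paragraph of the Discussion, limit the planned conclusion to executive function and describe the other domains as hypothesis-generating.
3. If the sponsor wants a confirmatory transfer claim, test the transfer measures with Holm's adjustment, and only after a significant 10-week primary result. With three measures the first step is at 0.05/3 = 0.0167; with digit span as one score it is at 0.05/2 = 0.025. Do not make transfer depend on the 3-month result as well: the sample size was set on the 10-week change, and a real effect that fades would leave transfer untestable.

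The cost is wording only: no new data or participants, and no loss of power for the primary test. The downside is that isolated secondary P values below 0.05 can no longer be claimed as effects and, under item 3, transfer faces a stricter threshold.
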